**Fig. 1 Fig1:**
[figure not shown]
Anticipated patient flow

### Adjustments of the study design during the course of the project

Some important modifications became necessary in the course of the project:

(1) Initially, when the project was conceptualized in 2017, five of the nine LVR-clinics decided to engage in the blended-care implementation study. As the number of refugees decreased in the following years, we recruited three more clinics. (2) The development of the App (subproject 2 of the I-REACH consortium) was delayed due to the COVID-19 pandemic. Consequently, the implementation study (subproject 4) was delayed. Recruitment of patients started in June 2022 with a delay of 16 months compared to the original plan. (3) Approximately six months after recruitment started, we decided to expand the inclusion criteria by including substance use disorders as an additional diagnostic group. (4) Initially, we had planned a cluster-randomisation with control group design in order to assess potential advantages of the blended care approach compared to treatment as usual (TAU). According to the original study design, half of the recruitment centers should offer TAU and recruit control patients. However, recruitment of a control group proved to be unfeasible in this trial: After six months of futile recruitment efforts, we decided to forgo the control group and focus on the main goal of the planned study, which had been the study of the implementation. Thereafter, the four control group centers were converted into intervention centers. The funding partner, ethics committee and Data Safety Monitoring Board (DSMB) approved this revision of the study concept.

### Intervention

Patients are offered the use of the “blended ALMAMAR” app during their inpatient stay in addition to routine care. The app (named ALMAMAR, Arabic for “path”) is based on CETA (Common Elements Treatment Approach) [19], a transdiagnostic therapeutic intervention that has already been evaluated in different settings and groups [e.g. 22–24]. CETA was adapted for the target group within subproject 2 of the I-REACH consortium [25]. Thereafter, the intervention was converted into a digital format (ALMAMAR) and thereafter, it was adapted to the inpatient setting (“blended ALMAMAR”). The adaptation process from ALMAMAR to “blended ALMAMAR” was performed by a multi-professional team from subprojects 2 and 4, which combined expertise in psychiatry, psychology and computer science. Each part (= “module”) of the app was checked for suitability for the inpatient context regarding (a) fitting to needs of inpatient care, (b) content, (c) complexity, (d) interactive character of the exercise, (e) duration, and e) phrasing.

The “blended ALMAMAR” app is able to stand alone (stand-alone self-management). Hence, patients may work with the app independently from the direct feedback of their therapists. The “blended ALMAMAR” version of the app was developed as an information and/or psychoeducation tool, and as an aid for the communication between therapist and patients. By reading information texts offered digitally in their native language and completing worksheets, patients can identify stress factors and resources, and they gain information about their mental illness. Therapists have the opportunity to view the digitally completed worksheets of their patients and receive valuable information that they can use in face-to-face-therapy, if necessary with the support of an interpreter. As automatic translation was not integrated into the app and Arabic and Farsi speaking practitioners or interpreters are not available 24/7 in routine inpatient mental health care, we had to ascertain that patients do not use the app for messages to their therapists, e.g. about suicidal thoughts. Accordingly, we did not allow free text entries within the “blended ALMAMAR” app. Instead, patients choose between predefined answer categories.

### Adaptations from the original CETA

Altogether, the “blended ALMAMAR” app for the inpatient setting comprises seven modules: *introduction, cognition, difficult memories, activities, substance use, relaxation techniques*, and *closing* (see Table 1 for details and adaptations from the original CETA). Two modules from the original CETA manual requiring direct interaction or free text entries (e.g., writing a letter to a friend) (modules “safety” and “exposure”) were not transferred into the blended ALMAMAR app. Both modules are performed in a face-to-face setting during inpatient treatment, if indicated. Additionally, some more complex and interactive cognitive exercises from the CETA manual were not adapted for the “blended ALMAMAR” app. In contrast to the original CETA program, there is no predefined order (‘flow’) or frequency of module usage by patients. Depending on the individual needs of their patient, therapists may choose between a standardized flow of modules and exercises for a specific mental disorder (e.g., depression flow, addiction flow etc.) and an individual flow consisting of an introductory module and other modules and exercises that can be added from a list (‘module pool’). Adaptations of the chosen flow are possible throughout the treatment. The duration of usage of the app is not predefined. The “dosage” prescribed (= number of modules and exercises selected by the therapist for the patient) depends on the clinical judgment of the therapist, there is no maximal or minimal dosage needed. The therapists are able to monitor the progress in the app usage of their patients and they can see all ratings of their patients in the German language (due to the predefined answers, the app can also show the Arabic/Farsi answers in German). Patients are able to continue working with the app during their inpatient stay, independent of face-to-face feedback from the therapist. The app can only be used during inpatient stay and is deactivated at discharge by the therapist. At discharge or in case of dropout, therapists have to manually select the module ‘closing’ in the app which contains a summary of all modules that the patient worked on as well as concluding words and all patient questionnaires for the post assessment.

**Table 1 Tab1:** Overview of the modules and content of the blended ALMAMAR app

No	Module	Content	Adaptation from original CETA
1	Introduction and explanation “blended ALMAMAR” app, overview of the planned modules	Overview of the goal and benefits of the “blended ALMAMAR” app as well as the modules. In addition, possible concerns and barriers to treatment are presented using pre-defined categories. Patients can select categories that apply to them by clicking on them. The module contains the questionnaires Baseline, which have to be filled out by the patients.	Adaptation of “encouraging participation” by using predefined categories; “introduction” was adapted to context of inpatient setting
2	Cognition: explaining the relationship between thoughts, feelings and behavior.	In this module, knowledge about the connections between thoughts, feelings and behavior is conveyed using example situations. Feelings and behaviors resulting from “helpful” and “unhelpful” thoughts will be reflected. The users can choose from predefined lists of example situations, corresponding thoughts and behaviors that they are familiar with or would be willing to try out.	Some of the more complex/interactive cognitive tasks were omitted (“thinking in a different way”; “family/friend role play”; “letter to a friend”; “responsibility pie”)
3	Difficult memories (lifeline)	Here, knowledge is imparted about the connections between important life events and feelings and behavior. It is possible to create a “lifeline” with significant (positive and negative) life events. Using predefined lists, life events can be selected and transferred to a timeline. The life events can be evaluated in terms of their significance.	“Lifeline” was used with predefined categories. We chose to add positive events to the exercise.
4	Behavioural activation (part 1 and part 2)	Part 1: Here, knowledge about the importance of stress-reducing activities is provided and a list of pleasant activities can be created based on predefined categories. For each entry on the list, lists of obstacles to this activity and possible solutions (again, selection from predefined categories) can also be created. The activity can then be entered into the calendar. Scheduled activities then appear in the calendar. Part 2 of this module includes an assessment of the completed activity selected in Part 1. Patients then have the opportunity to plan and complete the activity from the previous week or a new activity.	Only predefined categories of activities are used.
5	Substance use (part 1 and 2)	This module is about, teaching the connections between use (alcohol consumption/drug use/gambling addiction) and mental health impairments, feelings that arise before, during, and after substance use/gambling as well as positive and negative effects of substance use/gambling addiction. The module also aims to change attitudes/behaviors regarding substance use/gambling addiction. Patients have the opportunity to select a strategy/technique/interactive exercise (letting the urge go away, finding new activities, etc.). Patients can also repeat exercises and do more exercises (part 2 of the module).	The “addiction information sheet” is not used, all other exercises are carried out with predefined categories
6	Relaxation techniques (part 1 and part 2)	In this module, knowledge about different relaxation techniques is imparted. At the beginning, it is possible to choose from a list of relaxation techniques which techniques are already familiar. Each relaxation technique is rated on how helpful it is/was. Two relaxation techniques (Breathing and Grounding) are also integrated as audio files and can be performed afterwards and scheduled in the calendar. The exercise then appears in the calendar.	The relaxation techniques are presented through audio files.
7	Finishing steps	Summary of the completed modules. The module also contains the questionnaires that patients are asked to complete at the time of discharge. In addition, patients rate whether they have learned anything by using “blended ALMAMAR” during inpatient treatment.	“Talking about next steps” had to be omitted (patients have no access to the app and no contact to the therapist after discharge).

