### Recruitment, participant timeline and informed consent

The recruitment phase started in June 2022 and is planned for 31 months (until December 2024). Physicians and psychologists who work as therapists in the wards and day-clinics of the eight LVR hospitals can participate in the study as treatment providers for the “blended ALMAMAR” app (“therapists”). To familiarize therapists with the app “blended ALMAMAR”, a training course for therapists (two hours) was developed. Having participated successfully in this course, therapists obtain access to the app by an individual account. Therapists recruit patients during inpatient stay (see Fig. 1). Patients can be recruited shortly after admission or at some later point during their inpatient stay. After checking the inclusion and exclusion criteria, therapists hand out study information to suitable participants. A demo version of the “blended ALMAMAR” app can be shown for illustration if needed. Written informed consent sheets are available in Arabic, Farsi and German and interpreters can be consulted. Within the informed consent process, patients will be asked whether they agree to be contacted in case of dropout for participation in an ancillary study of the I-REACH consortium which examines reasons for dropout (“Prediction and prevention of dropout in research, diagnostics, and treatment with refugees”; PrevDrop). In case of consent, a separate informed consent is obtained by the participant for their participation in a qualitative interview. After written informed consent has been obtained, therapists give patients access to the “blended ALMAMAR” app to use it in addition to routine care (i.e., a setting blended of smartphone and personal contacts). All participants of the study fill out standardized questionnaires in Arabic or Farsi at study inclusion (t0: baseline assessment), upon discharge from inpatient treatment (t1: post assessment), and six months after discharge (t2: follow-up assessment). There is no predefined length of participation in the study since the duration of inpatient stay may vary largely between patients. At t0 and t1, questionnaires are delivered via the app. Follow-up assessments (t2) are conducted by telephone or via video call by the therapist (if necessary, with the help of an interpreter). In order to ascertain a high call back rate, therapists note the contact details of patients at discharge and can already fix a date for the planned interview.

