### Assessments and outcomes

The main hypothesis of the study is that the “blended ALMAMAR” app can be successfully implemented in inpatient psychiatric-psychotherapeutic care of refugees, and that it is accepted and used by therapists and patients.

The *primary endpoint* will be the use of the “blended ALMAMAR” app during inpatient stay, measured by:

recruitment rate (proportion of eligible patients who signed a consent form to participate);app usage rate (proportion of recruited patients who use the app at least once);average number of modules completed in the app;average duration and frequency of use of the app.

*Secondary endpoints* are clinical assessments, as well as acceptability and usability of the intervention. These will be assessed using questionnaire data from patients and therapists at each of the three time points (baseline assessment at study entry t0, post assessment at discharge t1, and follow-up six months after discharge t2; see Table 2 for an overview of all assessments).

**Table 2 Tab2:** Overview of the planned assessments

	Instrument	Who fills in?	Timepoint of measurement			Estimated duration (minutes)
No.			T0: Baseline (Admission)	T1: Post (Discharge)	T2: Follow-up (six months after discharge)	
1	Sociodemographic data	Patient	x			10
2	User rating of the app (CSQ-8) [30]	Patient		x	x	5
3	Post Migration Living Difficulties Checklist (PMLD) [26]	Patient	x			10
4	Expectation of therapy	Patient	x			5
5	EQ-5D-5 L (Health-related quality of life) [27]	Patient	x	x	x	5
6	*Health care utilization [selected questions from FIMA* [28] *and FIMPsy* [29]:					
	Number and specialisation of outpatient physician contacts in the last six months before inpatient admission (or baseline) and in the six months after discharge	Patient	x		x	3
	Number of inpatient stays and treatment days in the last six months before inpatient admission (or baseline) and in the six months after discharge	Patient	x		x	3
	Diagnoses, medications	Patient	x		x	3
	Number of visits to emergency departments in the last six months before hospitalization (or baseline) and in the six months after discharge	Patient	x		x	1
	Current employment [yes/no]	Patient	x		x	3
7	Main diagnosis of mental disorder and secondary diagnosis(es)	Therapist	x	x		1
8	Number of inpatient psychiatric treatment days and stays in the last six and twelve months, respectively	Therapist	x	x	x	3
9	Symptom severity (CGI) [31] and functional ability (GAF) [32]	Therapist	x	x		5

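### The patient acceptability rating (adapted CSQ-8) is not shielded from the therapist: at follow-up the therapist takes it in a live call, and at discharge the app appears to show it to the therapist

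*Protocol article*

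**What the plan says.** All references are to the protocol article.

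- **Role of the rating.** Assessments and outcomes makes acceptance by patients and therapists part of the main hypothesis and lists acceptability among the secondary endpoints. The patient instrument is the row "User rating of the app (CSQ-8" in Table 2, completed by the patient and marked at T1 (discharge) and T2 (six months later). The text below the table names it only at discharge.
- **Discharge.** Recruitment, participant timeline and informed consent states: "At t0 and t1, questionnaires are delivered via the app". Adaptations from the original CETA adds that the therapist has to select the closing module by hand, and that this module holds "all patient questionnaires for the post assessment". Table 1 confirms this for the last module: "The module also contains the questionnaires that patients are asked to complete at the time of discharge". The same row has patients rate whether they learned anything from the app.
- **What the therapist sees.** Adaptations from the original CETA says of therapists that "they can see all ratings of their patients in the German language", and explains why this is possible: "due to the predefined answers, the app can also show the Arabic/Farsi answers in German". The Intervention section also says: "Therapists have the opportunity to view the digitally completed worksheets of their patients".
- **Six months.** "Follow-up assessments (t2) are conducted by telephone or via video call by the therapist", with an interpreter if needed. Table 1, in the row for the last module, says that patients have no contact with the therapist once discharged.

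**The concern.** The therapist recruits the patient, opens the app, chooses the modules and, at discharge, is still treating the patient. A patient who knows or suspects that this person will read or hear the rating has a reason to be polite. The expected pull is towards higher satisfaction, which is also the direction of the study's hypothesis.

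The control group was given up (Adjustments of the study design during the course of the project). The acceptability result is therefore an absolute level in one group, and no comparison can cancel an inflation common to all patients. If the level is too high, the study may report that patients accepted the app when part of the score is courtesy to the therapist.

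**Working it through.** No formula applies. The article gives no CSQ-8 mean, standard deviation, threshold or mode effect, and it states no figure on this point to reproduce. The check traces the rating through the document.

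**Step 1: which ratings exist.** Table 2 has the CSQ-8 at T1 and T2. The text under the table has it at discharge only. The T2 rating therefore rests on Table 2 alone.

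**Step 2: who can see the T1 rating.**
- It is given in the app, inside the closing module, which the therapist must open.
- Therapists can see all ratings of their patients, in German. The stated reason, predefined answers, would apply equally to a questionnaire with fixed response options.
- Table 2 itself calls the CSQ-8 a user rating, so it falls within the literal wording.
- Data management and data access and Confidentiality deal with storage, export and identification. Neither limits what the treating therapist sees.
- *Broad reading* (all ratings includes the closing questionnaires): every T1 rating is visible to the therapist.
- *Narrow reading* (ratings made in exercises only): no T1 rating is shown to be visible.

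**Step 3: who takes the T2 rating.** The T2 assessment is a live call by the therapist. Any T2 CSQ-8 is thus spoken to the therapist, on either reading of Step 2. This takes "Follow-up assessments (t2) are conducted by telephone or via video call by the therapist" to mean the patient's own therapist. That is the natural sense, since the same section has therapists note contact details at discharge and allows them to fix the interview date.

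**Step 4: how many ratings.** The Sample size section aims at 100 patients with 20% dropout: 100 × (1 − 0.20) = 80. If that dropout applies to T2 (an assumption, as the article does not tie it to a time point), about 80 T2 ratings are affected, which is all of them. At T1 the share is 100% on the broad reading and 0% on the narrow one.

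**Step 5: what depends on the rating.** The primary endpoint consists of recruitment rate, usage rate, modules completed, and duration and frequency of use. These come from recruitment documentation and log-in data (Statistical methods for primary and secondary outcomes), and none uses the CSQ-8. The planned pre-post tests cover CGI, GAF and health-related quality of life. No CSQ-8 test, pooling or T1 to T2 comparison is described.

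**The case against.** The strongest case on the other side has five parts.

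1. *The discharge part is ambiguous.* The sentence on ratings is about monitoring patients' progress in the app, and the Intervention section gives worksheets as what therapists view for face-to-face work. Modules contain their own ratings, for example of relaxation techniques and life events. Detailed viewing rights may sit in the app manual or the data protection concept, which are not shown. This stands: the T1 part is a plain reading of the text but not an established fact.
2. *Dependence is weak at six months.* The patient is no longer in this therapist's inpatient care, and Table 1 even says contact has ended. This stands in part. Courtesy to a former therapist in a live call remains plausible, and the Table 1 statement conflicts with the planned call.
3. *Bias is not demonstrated.* Correct. Direction and size are inferred, and at T1 the effect also requires patients to believe that the therapist sees the answers. The article does not report what they are told about this.
4. *The endpoint is secondary and descriptive.* Correct, and it limits the importance of the point. Acceptance by patients is nevertheless part of the main hypothesis, and the CSQ-8 is the only patient acceptability instrument in Table 2. The learning rating in the closing module has the same exposure.
5. *A change now mixes collection conditions.* Recruitment has run since June 2022, so some ratings may already have been collected. This is a real cost, and flagging those ratings deals with it.

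A reader might go further and infer that the rating is never private and that acceptance is certainly overstated. The documents do not support this: the first depends on the broad reading at T1, and the second has no figure behind it. Nor is there a planned pooling or T1 to T2 comparison of the CSQ-8 to criticise.

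**Conclusion.** The point holds in limited form. As written, nothing protects the acceptability rating from the therapist. At T2 this is so for every rating taken, provided Table 2 is right that one is taken and the caller is the patient's own therapist. At T1 it is so for every rating if the wording on visible ratings includes the closing questionnaires, and for none if it does not.

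Upward bias is likely, on the ordinary assumption that patients answer more favourably to the clinician concerned. Its size cannot be derived from the article. It affects a secondary endpoint and the patient-acceptance part of the main hypothesis. It does not affect the primary usage endpoints, and it does not show that the app is poorly accepted. The sponsor should correct it because the main remedy is small and the result has no comparator to lean on.

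**What to change.** 1. State that therapists cannot view the CSQ-8 or the closing module's learning rating, set the app accordingly, and tell the patient so on the screen before these items. If the ratings are already hidden, say so in the protocol and add the on-screen sentence.
2. Name the self-completed discharge CSQ-8 as the main acceptability measure.
3. Report any six-month CSQ-8 separately and label it therapist-administered. Where possible without extra staff, have it asked by existing study staff who did not treat the patient. The local coordinators are candidates, but the article does not say whether they are outside the treating team.
4. Flag ratings collected before the change and show them separately.
5. Reconcile the text under Table 2 with Table 2 itself on whether the CSQ-8 is taken at six months, and the no-contact statement in Table 1 with the therapist's follow-up call.

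**Cost.** A small app change (how small is an assumption, since the article does not describe the app's settings), a sentence on screen and a short amendment. Ratings will exist under two visibility conditions, and the six-month rating will carry less weight. Dropping the six-month CSQ-8 altogether is not free, because it would remove the only follow-up acceptability rating in Table 2. Separate reporting is therefore preferable.
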